### Statistical analyses

#### Qualitative data and mixed methods integration

Qualitative data from the family interviews and periodic reflections will be analyzed using a rapid qualitative data analytic approach guided by the domains of PRISM [29]. Specifically, we will develop a matrix of summary responses from the qualitative data sources. A codebook will be developed from this matrix and used on all transcripts, allowing for both a priori and emergent themes. Coding will be completed by a qualitative analytic team and a small group of trained research team members. A subset of data will be group coded for consensus-building followed by independent coding, team-based review of codes, and further refinement of the codebook, as needed. The rest of the transcripts will be independently coded with 10% of them being double coded to verify acceptable inter-rater reliability (>70% consensus). We will also engage the CARAB group in reviewing the coded data to support sense-making and develop action items based on the data to identify refinements prior to each rollout. We will use a joint display analysis [45] to support the integration of survey and qualitative data sources for the purposes of comparison, complementarity, and expansion [75–77].

#### Adaptations documentation data

We will use the Stirman et al. [43, 70, 71] Adaptations framework (FRAME-IS) to characterize adaptations identified throughout the study period using the adaptations tracker. The research team will meet monthly to review the Adaptations tracker and determine whether any adaptation requires immediate action to support implementation optimization.

#### Quantitative data

Primary analyses for Aim 2 will assess fidelity and reach outcomes (Aim 2b) assessed within the EHR (e.g., screening, referrals, and follow-up assessments) and surveys (e.g., Acceptability, Feasibility, and Appropriateness) across the study period using Generalized Linear Mixed-effects Models (GLMM) and time-varying indices for clinics randomized to cross-over in each wave, time (secular trend), and clinic characteristics as planned covariates. Serial cross-sectional summaries for each clinic within monthly blocks will allow estimation of changes in clinic outcomes after crossing over into interventions. Primary analyses for Aim 3 will describe I-FRESH participants’ (*n* = 240) changes in health outcomes including: a) metabolic labs, BP, BMI, b) healthcare utilization; c) community program utilization; d) Quality of Life; e) Food Frequency Questionnaire and f) Knowledge, Skills, Attitudes, and Self-Efficacy. GLMM growth models for individual trajectories of continuous and limited categorical outcomes will include a focus on significance of changes from baseline to post-treatment assessments after graphically examining an appropriate functional form (e.g., linear or categorical) for modeling each outcome. All models will include participants’ characteristics (gender, ethnicity, parental education) and allocation clinic as planned covariates when estimating changes in primary health and engagement outcomes. We will explore the role of SDOH and implementation strategy effectiveness as potential influences in describing changes in parent and child health outcomes. Benjamini-Hochberg [78] procedures will be used to adjust *p*-values for inference decisions within common domains.

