**Trial registration:**

NCT06661538.

Contributions to the literature• The Roll-Out Implementation and Optimization trial design allows us to quickly and continuously learn and adapt workflows across sites and identify effective strategies to implement a food insecurity screening and referral process that is not confounded by time and system-level changes.• This design allows us to examine the impact of strategies within clinics over time and between clinics at each time point.• This study uses community engagement methods to gather healthcare providers and staff, community-based nutrition support programs, and implementation science researchers to address the complex issue of connecting patients with health-related social-needs to appropriate community programs.

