Once the program is implemented in each clinic, we will conduct periodic reflections [34] with key stakeholders, including families, and the CARAB to allow for real-time iterations in program implementation. These reflections will occur before, during, and after roll-out of the intervention in each of the 4 clinic sites. Roll-outs in each new clinic will occur every 4 months. We will use a modified Stirman Framework [43] to track adaptations monthly [44]. Documentation of adaptations will include brief multilevel surveys with staff and key stakeholders. Semi-structured interviews or focus groups with key stakeholders and families will occur at 3 and 6 months to expand on written adaptations. Data from all sources will be triangulated using joint display analysis [45] to determine which adaptations should be included as permanent implementation strategies in the next clinic iteration

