##### Power considerations

We conducted power/sample size for this ROIO design trial to address primary aims, using developed formulas [81] drawn from stepped wedge designs that account for unequal cluster size and package *swCRTdesign* [82]. The design includes 4 identified clinics (clusters), at least one 3-month period in standard care and 4 additional periods where assigned clinics can transition to I-FRESH at 4-month intervals. We estimated the needed sample to test a 10% difference in proportions of engagement in services (i.e., Aim 2b healthcare and community program utilization), and a standardized mean increase of at least d ≥ 0.20 when reported at 6- and 12-month health outcomes. With alpha = 0.05, 4 clusters (1 clinic per cluster = 4 clinics with *n* = 300 - 500 potential patients in each clinic) and five periods of transitions (baseline and 4 clinics), we will maintain power > 0.83 to detect clinic differences (I-FRESH vs standard care) of >8% in rates of screening, referral and follow-up engagement in services and changes in acceptability ratings of d > 0.20 after implementing I-FRESH given a between clinic standard deviation of 0.05 in random treatment effects. Using an empirical approach, we simulated 1000 data sets with expected mean changes (d ≥ 0.20) and serial correlations similar to pilot samples. We used the percentage of growth models with *p* < 0.05 for slope parameters to estimate power given proposed sample of 60 per clinic and allowance for 20% missing data. With median slope of 0.02 (increase per month; estimate sd = 0.01) we observed significant effects in >81% of models suggesting sufficient power to detect desired effects in Aim 3 with the proposed sample.

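### The Aim 2 model and its power target fit an effect that does not change after cross-over, although the programme is revised within and between clinics; strategy version is also aliased with clinic and order

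*Protocol article*

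**What the plan says.** **Model.** Under Quantitative data, the primary Aim 2 analysis is a GLMM with "time-varying indices for clinics randomized to cross-over in each wave, time (secular trend), and clinic characteristics as planned covariates". No term for time since cross-over or for programme version is named. Monthly cross-sectional summaries per clinic are also planned. Strategy effectiveness is only explored, and only for parent and child health outcomes.

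**Power.** Under Power considerations: "we will maintain power > 0.83 to detect clinic differences (I-FRESH vs standard care) of >8% in rates of screening". The only allowance for varying effects is a between-clinic SD of 0.05 in random treatment effects.

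**Programme.** Specific Aim 1 plans periodic reflections with stakeholders, families and "the CARAB to allow for real-time iterations in program implementation". The Fig. 1 legend adds refinement before each clinic, the Fig. 2 legend allows any component or strategy to be modified, and Adaptations documentation data provides a monthly review that can trigger immediate action.

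**Claim.** The contributions statement after the abstract says the design makes it possible to "identify effective strategies to implement a food insecurity screening and referral process that is not confounded by time and system-level changes".

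**The concern.** A cross-over indicator with a secular trend estimates one number for all treated clinic-months. That suits a treatment whose effect is the same in its first month as in its twelfth. Here the programme is meant to be improved while it runs, so growth with exposure is a pattern the analysis should be able to show. In a stepped wedge, clinics that crossed over earlier serve partly as comparators for those that cross later. Growth in the early clinics is then partly read as secular trend and subtracted.

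The second issue is attribution. The four clinics are diabetes, gastroenterology, preventive cardiology and severe asthma, one per step, and each starts with its own version of the strategies. A between-clinic difference cannot be assigned to version rather than to specialty or roll-out date.

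At stake is what the trial can say about the size of the programme's effect, and about which strategies produced it, when the later hybrid trial is planned.

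**Working it through.** **1. The plan's own figure.** Stated inputs: "With alpha = 0.05, 4 clusters"; "1 clinic per cluster = 4 clinics with *n* = 300 - 500 potential patients in each clinic"; five periods; treatment-effect SD 0.05; difference 8 points; power above 0.83. The article gives no baseline rate or clinic SD, and does not say whether 300-500 is per period or in total. I assumed a linear mixed model with fixed periods, baseline rate 0.1-0.5, clinic SD 0-0.10 and two-sided alpha.
- 8 points, 300-500 per clinic-period: power 0.65-0.83.
- 8 points, 300-500 in total (60-100 per period): 0.29-0.63.
- 10 points (the paragraph also says "We estimated the needed sample to test a 10% difference in proportions of engagement in services"), 300-500 per period: 0.83-0.95.

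The stated power cannot be uniquely reproduced, but some inputs reach it. It is not shown to be wrong.

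**2. What the on/off coefficient averages.** Calendar: 3 months of standard care plus 4 x 4 months = 19 months, with cross-over after months 3, 7, 11 and 15. The model is clinic intercept + time + θ·(on/off). The estimate is a weighted sum of clinic-months, with weights from the last row of (D'V⁻¹D)⁻¹D'V⁻¹, where D is the design matrix and V the covariance. Its expectation is Σ(weight × true effect) over treated months, and those weights sum to 1.

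The 40 treated clinic-months fall in exposure bands of 16, 12, 8 and 4 months. Total weight per band, categorical time, by clinic-to-residual variance ratio:

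| Ratio | Months 1-4 | 5-8 | 9-12 | 13-16 |
|---|---|---|---|---|
| 0.05 | 0.755 | 0.300 | 0.023 | -0.077 |
| 1 | 1.00 | 0.30 | -0.10 | -0.20 |
| 1000 | 1.036 | 0.300 | -0.118 | -0.218 |

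**3. Effect patterns (assumed; the article gives none).**
- *Constant 8 points:* the estimate is 8.0 at every ratio.
- *Rising with exposure, 4, 8, 12, 16 points by band:* the mean over treated months is (16×4 + 12×8 + 8×12 + 4×16)/40 = 320/40 = 8.0. At ratio 1 the estimate is 4×1.00 + 8×0.30 − 12×0.10 − 16×0.20 = 2.0. From ratio 0.05 to 1000 it runs from 4.45 to 1.64 (categorical time) or 4.64 to 2.06 (linear time). At ratio 0.01 it is 5.6-5.7.
- *A plausible ratio:* clinic SD 0.05, baseline rate 0.3 and 100 patients per clinic-month give 0.0025/(0.3×0.7/100) = 1.19. The estimate is then 1.95 (categorical) or 2.34 (linear).
- *Rising only from clinic to clinic, 4, 8, 12, 16:* the mean is again 8.0 and the estimate 7.6-10.4 over ratios 0.05 to 1000.

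**4. Does a random treatment effect by clinic repair this?** I added one with variance equal to the clinic variance. The exposure-ramp estimate is then 2.0-4.3 over the same ratios, so it does not.

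**5. Version against clinic.** With one clinic per step, a set of version terms is the same as a set of clinic-specific effects. If instead each version applies system-wide by calendar period, the design matrix has rank 11 of 12. The last version's effect is then not estimable, because no clinic remains in standard care. If the plan's SD of 0.05 is read as clinic variation unrelated to version, two clinics must differ by 1.96 × 0.05 × √2 = 0.139, about 14 points, before version becomes a needed explanation, even with unlimited patients.

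**6. Price of exposure-time terms.** Five periods, assumed baseline rate 0.3, clinic and treatment SD 0.05, 400 patients per clinic-period. The SE is 0.031 on/off and 0.046 for the average over four exposure bands. Power at 8 points, Φ(0.08/SE − 1.96), is 0.73 and 0.42 (unrounded SEs 0.0311 and 0.0455).

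**The case against.** **The model wording leaves room.** The plural indices per wave could mean wave-specific terms, the monthly summaries give a view of change after cross-over, and exact coding is normally left to an SAP. This stands in part. But wave-specific terms would coincide with clinic and would not capture change within a clinic, and the article itself names the covariates and the powered contrast.

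**The bias is conditional and the ramp is invented.** This stands. No section gives an effect pattern. A constant effect is estimated correctly, and clinic-to-clinic improvement, which is the core of the roll-out design, stays fairly close to its mean. The lowest figure, 1.6, needs a very large variance ratio.

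**Strategies are not chosen from this coefficient.** This also stands. A reader might infer that an improving programme will be reported as ineffective and the wrong bundle carried forward. The article does not support that: Specific Aim 1 selects adaptations by triangulating all data sources in a joint display, with advisory-board review, and no between-clinic test of versions is planned.

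**Specialty is neither time nor a system-level change.** That is fair as a reading of the contributions statement, and the secular term does adjust for common trends. But the statement concerns identifying effective strategies, and version follows roll-out order, which is itself time.

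**Conclusion.** The concern holds conditionally. The named Aim 2 terms and the single powered contrast assume an effect that does not depend on time since cross-over, and the design gives good reason to expect that it might. Under an assumed 4-to-16-point ramp with exposure, the coefficient is about 1.6-4.6 points against a mean of 8.0 for variance ratios of 0.05 and above. These sizes rest on assumed effect patterns and variance ratios; the uneven, partly negative weighting of exposure time comes from the layout and the model. Nothing here shows that the coefficient will be wrong, or that the stated power is. Separately, version, clinic and roll-out order cannot be told apart with one specialty clinic per step, so the contributions statement claims more than the design can deliver.

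**What to change.** 1. Keep the planned Aim 2 model. State that its coefficient is a weighted average over programme versions and exposure times, with the weights set by the layout.
2. Pre-specify a supporting Aim 2 analysis with 4-month exposure-time bands. Report each band and the average over bands beside the on/off estimate.
3. Label between-clinic version comparisons as descriptive. Do not use a trend over roll-out position to estimate optimisation: it is the same between-clinic contrast across four specialties.
4. Narrow the contributions statement to adjustment for secular trends common to all clinics while some clinics are still in standard care.

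**Cost.** Wording and a few model terms, using the monthly data already planned. The band average is less precise (SE about 0.046 against 0.031, power at 8 points about 0.42 against 0.73 under the inputs in step 6), and the plan should say so. That is why it is proposed as supporting and not primary. The last band rests on the first clinic alone, and the bands assume the same exposure curve in every clinic.

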Aim 3 Effectiveness Outcomes	• Health outcomes: BMI/weight status, HbA1c, blood pressure, total cholesterol, HDL cholesterol, liver function, health status • Quality of life, stress, well-being • PRAPARE (patient assets, risks, and experiences) • Medications (including dose) & Health care utilization • Community program utilization (including barriers & facilitators) • Knowledge, Skills, Attitudes, Self-efficacy • Food Frequency Questionnaire [68] • Demographics: Race/ethnicity, age of child and parent, sex and gender identity of child and parent, address, zip code, birthplace, current employment status, educational attainment, annual family income, health insurance • SDOHfactors: Food insecurity, health literacy & numeracy, access to health services, access to health technology, internet access, job insecurity, housing insecurity, discrimination, discrimination in health care, food swamp	Ch P P Ch P P P P, Ch P	EHR Survey Survey EHR Survey Survey Survey Survey, EHR Survey	0, 6, 12 mos 0,12 mos 0,12 mos 0,12 mos 0,12 mos 0, 6, 12 mos 0, 6, 12 mos 0 mos 0, 12 mos

The PRISM Fit Assessment [72–74] will be conducted before each new roll-out of a clinic which examines how well the current implementation strategies align with the new clinic and whether it will reach similar RE-AIM metrics as in the previous clinic implementation. Representative clinic providers and staff, community stakeholders and hospital administrators will complete this 21-item survey using the iPRISM web tool (prismtool.org) before each clinic roll-out. Results will be reviewed during a CARAB meeting and additional refinements to the implementation strategy will be made.

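### The Aim 3 power of >81% is counted at unadjusted p < 0.05, so it is per-outcome power and not the power of the planned Benjamini-Hochberg rule

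*Protocol article*

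**What the plan says.** Two parts of the Statistical analyses section of the protocol article bear on this.

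- **Decision rule (Quantitative data).** The closing sentence says that Benjamini-Hochberg adjusted p-values will serve for "inference decisions within common domains". The Aim 3 outcomes come in six groups, a to f, beginning "a) metabolic labs, BP, BMI, b) healthcare utilization; c) community program utilization; d) Quality of Life". Table 1 itemises the first kind as "Health outcomes: BMI/weight status, HbA1c, blood pressure, total cholesterol, HDL cholesterol, liver function, health status". The article does not say which outcomes form a domain or which false-discovery level applies.
- **Power (Power considerations).** For Aim 3, "we simulated 1000 data sets with expected mean changes (d ≥ 0.20) and serial correlations similar to pilot samples", and then: "We used the percentage of growth models with *p* < 0.05 for slope parameters to estimate power", with 60 parents per clinic and 20% missing data. More than 81% of models were significant, and the article concludes that the sample is adequate for Aim 3. The Aim 2 calculation begins "With alpha = 0.05, 4 clusters" and reports power above 0.83 for differences in screening, referral and follow-up rates and for changes in acceptability ratings. Neither calculation mentions a multiplicity adjustment.

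Aim 3 is called preliminary in the specific aims and exploratory in the Aim 3 description.

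**The concern.** A power figure tells the reader how often the planned analysis will declare an effect that is really there. Here the analysis declares effects on adjusted p-values, while the simulation counted unadjusted ones. A Benjamini-Hochberg adjusted p-value is never smaller than the raw one. At the same 0.05 level, a domain with two or more outcomes therefore cannot have higher power per outcome than the raw test. Group a (laboratory values, blood pressure, BMI) plainly holds several outcomes.

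What is at stake is how the results will be read. The Aim 3 models are planned with a focus on the significance of change from baseline, and the results feed the design of a fully powered hybrid trial. A reader told that power exceeds 81% may give too much weight to an outcome that is not significant after adjustment. The stated margin over 80% is about one point, so a small loss uses it up.

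**Working it through.** **Inputs from the article.** Slope test at p < 0.05 (two-sided assumed, as sidedness is not stated); d = 0.20; 4 × 60 = 240 families, or 240 × 0.80 = 192 after 20% missing data; stated power >81%.

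**Inputs assumed.** Number of outcomes per domain m (2 to 7; Table 1 lists about seven health outcomes); number k that truly change; false-discovery level q (0.05, then 0.10); independent tests unless noted.

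**1. Is >81% consistent with an unadjusted test?** The serial correlations are not given, so the simulation cannot be reproduced exactly. A paired-change approximation is

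power = Φ( d·√n / √(2(1 − r)) − 1.96 ).

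With d = 0.20 and n = 192 it gives 0.716 at r = 0.4, 0.791 at r = 0.5, 0.807 at r = 0.52 and 0.873 at r = 0.6. The stated figure therefore fits an unadjusted two-sided 0.05 test with a correlation a little above 0.5.

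**2. Carry that power to the planned rule.** A test with 81% power at two-sided 0.05 has non-centrality 1.960 + 0.878 = 2.838. I simulated m normal test statistics, k of them with mean 2.838 and the rest with mean 0. The Benjamini-Hochberg rule rejects the j smallest p-values, where j is the largest rank with p(j) ≤ q·j/m. Power is the average rejection rate over the k true effects (at least 100,000 replicates).

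Level q = 0.05, independent tests:

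| Outcomes in domain | One changes | About half or more change | All change |
|---|---|---|---|
| 2 | 0.73 | – | 0.79 |
| 3 | 0.68 | 0.74 (two) | 0.79 |
| 6 | 0.59 | 0.69 (three) | 0.78 |
| 7 | 0.57 | 0.71 (four) | 0.78 |

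With correlation 0.5 between outcomes, the all-change figures are 0.78 for three and 0.76 for seven. A one-outcome domain stays at 0.81.

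**3. Vary what the article leaves open.**

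- Level q = 0.10, raw power 0.81: three outcomes give 0.77, 0.83 and 0.87 with one, two and three true effects; seven give 0.67, 0.81 and 0.87 with one, four and seven.
- Level 0.05, raw power 0.85 (allowed by >81%): about 0.83 if all change (three or seven outcomes); 0.77 if four of seven change.

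**4. Simulation noise.** For 81% from 1000 data sets, the 95% half-width is 1.96·√(0.81 × 0.19 / 1000) = 0.024.

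**5. Aim 2, only if the adjustment covers it.** Taking the three rates as one domain, with 0.83 per test, level 0.05 and independence, power is 0.70, 0.77 and 0.81 with one, two and three true effects.

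**The case against.** The strongest reply is that no stated figure has been shown wrong. The article gives its criterion openly, per-outcome power at p < 0.05 is a common planning quantity, and it never claims to be power after adjustment. This stands as far as it goes: the simulation result is not disputed. It does not rescue the conclusion drawn from it, since adequacy for Aim 3 is asserted while inference is to follow another rule.

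Second, the power premise is that outcomes change by at least 0.20 SD. If all of them do, the loss is about 2 to 3 points with independent tests, which is about the simulation's own Monte Carlo error. The large losses need most outcomes in a domain not to change. This also stands, and it limits the size of the point.

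Third, Aim 3 is exploratory, and domain membership and false-discovery level are details that an article may leave to the full plan. Agreed: their absence is not the complaint. It means only that the loss cannot be fixed from the article.

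A reader might infer more: that power is below 81% in every multi-outcome domain, that the true figure is 0.57 to 0.79, or that the Aim 3 claim fails. The document does not support these. They need raw power of exactly 0.81, when the article gives a lower bound, and a level of 0.05, which it does not state. At 0.10 several cases reach or exceed 0.81. Nor is it clear that the adjustment covers Aim 2: the sentence closes the section but follows a run of Aim 3 text.

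**Conclusion.** The mismatch is real. The >81% describes one outcome tested at unadjusted 0.05, while decisions will use Benjamini-Hochberg adjusted p-values within domains, at least one of which holds several outcomes. The adequacy statement for Aim 3 is therefore not supported for the rule that will be applied.

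The size is uncertain. With exactly 0.81 per test, a level of 0.05 and independent tests, power per changed outcome in domains of 2 to 7 is about 0.78 to 0.80 if all change and about 0.57 to 0.73 if only one does. A level of 0.10 or a raw power above 0.81 shrinks or removes the shortfall. These figures are an illustration, not an estimate for this trial. As Aim 3 is exploratory, the point calls for a correction to the power statement and does not threaten the validity of the trial.

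**What to change.** - State which outcomes form each domain and the false-discovery level.
- Re-run the existing Aim 3 simulation over the outcomes in each domain, with plausible correlations and with one, some and all outcomes changing. Count Benjamini-Hochberg adjusted rejections and report the resulting range in place of >81%.
- If the simulation is not re-run, label >81% as unadjusted power for a single outcome and qualify the statement that power is adequate.
- Say whether the adjustment covers the Aim 2 rates. If it does, treat the >0.83 in the same way.

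The illustrative ranges above should not be written into the protocol as the replacement figure, because they rest on assumed domain sizes, level and independence.

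The cost is a few hours of simulation and a short text change. The stated power may become less favourable. Sample size, design and data collection need not change.
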